### Procedure

An initial screening visit (by a trained researcher) will seek informed consent and confirm whether the participant meets the inclusion criteria. If the inclusion criteria are met, the timescale for the three time points of measurement will commence. (1) Baseline (within 2 weeks prior to the first session of the intervention), (2) 2 months post-baseline, and (3) 6 months post-baseline. Data will be collected during face-to-face sessions with the researcher. The carer will also be available to support the person with ID should this be requested/necessary. At the 6-month post-baseline visit, the researcher will conduct semi-structured one-to-one interviews with participants and carers who took part in the intervention.

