### Participants

Twenty participants will be recruited for the study. Inclusion criteria are (1) over the age of 18 years, (2) with an ID (established through the administration of the Wechsler Abbreviated Scale of Intelligence 2nd Edition [41]) and Adaptive Behaviour Assessment System© (ABAS; 2^nd^ Edition [42]), (3) have clinically significant difficulty with anger control as assessed by their clinician, (4) able to give informed consent, and (5) has a family member or paid carer who has supported them for a minimum of 6 months, is available to participate in the treatment sessions, and who currently provides a minimum of 2-h support per week to the participant. Although language ability is not an inclusion criterion, if participants are able to give informed consent, then they are also likely to have the language level needed to participate in an UMAA-LD SoF intervention.

Exclusion criteria are (1) existing diagnosis of autism spectrum disorder (because of potential difficulties with more abstract concepts relating to mindfulness when ID and autism are co-morbid), (2) presence of mental health problems or behaviour that may prevent the participant from interacting with the carer or therapist or retaining information from the therapy (e.g., dementia, active psychosis), and (3) individuals who are currently receiving direct psychological intervention (e.g. relaxation training, DBT, CBT).

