#### Feasibility process measures

To address aim 1, the following measures will be taken.Screening and recruitment rates will be monitored.The MAIDS to measure skills in using mindfulness to manage anger.Data on adherence to mindfulness home practice.Participant drop out from the feasibility study will be closely monitored and reasons gathered where possible.An assessment of the completion rates of the questionnaires will be completed. This will encompass an analysis of any missing data patterns.Information gleaned from the qualitative interviews will be used to inform understanding of the process.Intervention fidelity will be monitored. Two out of six sessions with each participant will be audio recorded. One will be from the start of the intervention (sessions 1–3) and the other from sessions 4–6. The recordings will be evaluated using an adaptation of Singh’s Soles of the Feet monitoring form that evaluates adherence to the Soles of the Feet manual [23].A clinical input questionnaire will capture the participants’ recent clinical input (e.g. from a behavioural specialist, any other direct psychological interventions) and be completed by the carer with the researcher during the consent visit, this is repeated during the baseline visit to identify any recent changes.

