#### Qualitative interviews

Qualitative semi-structured one-to-one interviews with participants and carers will be conducted after all outcome data have been collected (6 months after baseline) focusing on the interview topics described below.
*Participants:* How accessible/acceptable SoF meditation was, the impact upon their feelings and expressions of anger, their quality of life, adherence and perceived barriers to the intervention, use of the mindfulness practice audiofiles at home, whether they will continue to use SoF meditation, exploration of any relationship changes with their carer, and any future support needed.
*Carers:* Perceived impact of the intervention on their offspring/client, their relationship with their client/ family member throughout the intervention, and exploring what, if any, impact it had on their own lives, both personally and as a carer.
*UMAA-LD SoF therapists:* their experiences of mindfulness prior to training, their experience of being trained to use UMAA-LD SoF, experiences of delivering the UMAA-LD SoF, including the accessibility of the manual for themselves and clients and the perceived effects on participants and carers.

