#### Protocol for a full-scale effectiveness trial

To address aim 4, a full study would be considered feasible if (1) recruitment rate found was more than 50 %, (2) if the retention rate found was more than 50 % at final follow-up, and (3) if adherence rate was greater than 50 % for the completing participants.

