In health economics evaluations, the NHS traditionally prefers a cost-utility approach to economic analysis, whilst in Public Health cost-benefit and cost-consequence analysis are considered to be more appropriate by NICE [63]. The UMAA-LD SoF intervention may result in benefits and possible cost savings that goes beyond the health service; therefore, a public sector multi-agency approach to economic analysis is likely to capture this wider potential impact of the intervention.

There will likely be variability in therapists’ previous experience of practicing or teaching mindfulness-based approaches. The UK Good Practice Guidelines for teachers of mindfulness-based programmes such as MBSR and MBCT stipulate that those delivering MBIs have personal experience of mindfulness practice [64]. However, due to practicalities of recruiting ID health professionals to deliver UMAA-LD SoF, we will aim for this but anticipate this will not always be possible. Those who do not have personal experience of mindfulness practice in advance will be offered support and encouragement to develop this. Although this intervention is mindfulness informed, it is not mindfulness-based, because it does not comply with UK good practice guidelines (although these were developed for teachers of the 8-week courses for the general public or clinical populations and are not intended to be specific for ID populations [64]). This aspect of the project will be closely monitored as part of the feasibility study, through the qualitative interviews with the therapists, as the personal practice of the teacher and how this is embodied could be important with an ID populations as it bypasses cognitive verbal channels.

We anticipate that the qualitative information will enhance the quantitative analysis and RCT protocol. Although preliminary data on the effectiveness of the intervention will be taken, it will not give insight into the mechanisms of change. This question will be explored in the qualitative data, with participants, their carers, and with clinicians. The qualitative data will also help identify any practical barriers or facilitators to participating in the intervention and any unanticipated positive or negative affects of the intervention.

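### Participant and carer interviews are set only at the 6-month visit, so first-hand data on acceptability, barriers and negative effects come mainly from those retained

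*Protocol article*

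**What the plan says.** Two sections of the protocol article fix when participants and carers are interviewed. Procedure: "At the 6-month post-baseline visit, the researcher will conduct semi-structured one-to-one interviews with participants and carers who took part in the intervention". Qualitative interviews: these "will be conducted after all outcome data have been collected (6 months after baseline").

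The participant topics begin with "How accessible/acceptable SoF meditation was, the impact upon their feelings and expressions of anger" and go on to adherence and perceived barriers. Acceptability and accessibility are named in the first principal aim (Aims). The Discussion relies on the qualitative data to identify barriers, facilitators and "any unanticipated positive or negative affects of the intervention".

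For people who leave, Feasibility process measures states: "Participant drop out from the feasibility study will be closely monitored and reasons gathered where possible". Therapists form a third interview group, and their topics include "the perceived effects on participants and carers". The article does not tie their interviews to the 6-month visit.

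On numbers, "Twenty participants will be recruited for the study". A full trial is considered feasible on retention "if the retention rate found was more than" 50% at final follow-up, alongside criteria for recruitment and for adherence; the adherence criterion applies to completers only.

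**The concern.** Attending the 6-month visit is in effect a condition for giving an interview. People who leave before then are plausibly those for whom the intervention worked least well. They may have found it hard to follow, burdensome or unpleasant; the second and third meditations ask the participant to call an anger-provoking situation to mind. If so, the interviews under-represent the people best placed to describe barriers and unwanted effects.

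The Discussion says that all data collected will be used to revise the intervention protocol and, if the study is promising, that a package for a randomised trial will follow. A favourable picture drawn mainly from those who stayed could leave correctable problems in the manual. The other feasibility criteria do not fill the gap: none measures acceptability directly, and adherence is judged among completers.

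**Working it through.** The article gives no figure for interview coverage, so there is nothing to reproduce. The check has two parts.

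**1. Who can give first-hand data, taking the sections together**

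| Situation | 6-month interview (participant and carer) | Other information planned |
|---|---|---|
| Completes sessions, attends 6-month visit | Yes | Therapist interview |
| Stops sessions, attends 6-month visit | Yes: having taken part is required, completion is not | Therapist interview |
| Leaves the study before 6 months | No | Reasons for drop-out where possible; therapist's second-hand view |

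Only the third row is affected. A reason for leaving, if obtained, may touch on a barrier or an unwanted effect, but it does not cover the interview's topics.

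**2. How many could fall in the third row with the retention criterion met**

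Inputs: N = 20 (Participants); retention above 50% at final follow-up (Protocol for a full-scale effectiveness trial). Assumption: being retained means attending the 6-month visit.

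- Smallest r with r/20 > 0.50: 10/20 = 0.50 fails and 11/20 = 0.55 passes, so r = 11.
- Largest number absent: 20 − 11 = 9, and 9/20 = 45%.

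The documents state no expected drop-out, so a range is shown. The first three rows are assumed values; the last is the limit set by the criterion.

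| Retained at 6 months | Not interviewed because they left | Share of 20 |
|---|---|---|
| 18 | 2 | 10% |
| 16 | 4 | 20% |
| 14 | 6 | 30% |
| 11 | 9 | 45% |

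These count missing interviews. They do not measure bias in an acceptability rate: Method of analysis plans framework analysis of the interviews, which is thematic, and no interview-based acceptability percentage is planned.

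**The case against.** A reader might infer that people who withdraw are never asked anything. The article does not support that, since drop-out reasons are to be gathered where possible. A reader might also infer that all the acceptability evidence comes from the retained. That too goes too far: therapists are interviewed and can speak about people who left, and Method of analysis lists patient acceptance and adherence among the adherence outcomes. Nor does the gap reach everyone who stops treatment, because those who stop sessions but attend at 6 months remain eligible.

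The timing also has a rationale. Interviewing after outcome collection avoids discussing anger and impact with a participant before later outcomes are taken, and topics such as continued use of the meditation need some follow-up. Participants may withdraw at any time, so no interview can be required of them. A loss of 9 would be openly visible in the retention figure. Finally, a journal article may leave contact with withdrawers to the full protocol.

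Most of this stands and narrows the point without removing it. Drop-out reasons and therapists' views are thinner and, for therapists, second-hand. A visible retention figure says how many left, but not how they experienced the intervention. The timing is also not an unstated detail: two sections state it as a rule, and that rule selects on retention. The rationale for interviewing last does not apply to someone who will give no further outcome data.

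**Conclusion.** The point holds for those who leave the study before 6 months. As written, neither they nor their carers are interviewed, and first-hand evidence on acceptability, barriers and negative effects comes mainly from those retained. The criterion permits up to 9 of 20 (45%) to be missing in this way. That is a limit, not a forecast, and with 18 retained it would be 2. It rests on equating retention with attendance at the 6-month visit. That leavers hold less favourable views is plausible, but nothing in the article shows it, so neither the direction nor the size of any bias can be stated. The weakness is moderate and cheap to reduce, in a study whose purpose is to learn about acceptability before a trial.

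**What to change.** - Offer the existing interview to any participant who leaves the study before 6 months, and to the carer. Do this at the time of leaving, or later if they agree to contact. Make it voluntary, and say so in the information sheets, so that the right to withdraw is respected.
- Keep the 6-month interview for people who stop sessions but remain in follow-up, so that interviews still come after outcome collection.
- Report themes from early leavers separately, with the number not interviewed.

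Cost: small changes of wording in the protocol and information sheets. The maximum stays at 20 participant-carer interview sets with the same researcher, some of them done earlier. Some leavers will decline, so the gap shrinks but may not close. Their interviews will fall at a different time from the rest, and topics that depend on longer follow-up will be answered less fully. Reporting them separately makes both limits visible.

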#### Development of the UMAA-LD SoF protocol

The core SoF meditations [23] will be used in the UMAA-LD SoF manual. Singh et al. [23] provides a detailed description of how to teach Soles of the Feet mediation in the original manual. There are three main SoF meditations, all follow the same broad therapist instructions but with a different emphasis on the evoked emotion. The steps outlined below demonstrate typical therapist guidance during a SoF meditation (step 2: adapted from [23]):Sit or stand in a natural position with the soles of the feet flat on the floor.Breathe naturally.Think about an incident that made you feel angry.Notice the angry thoughts and stay with them, just notice how your body feels, and any thoughts or emotions that are around.Quickly shift the focus of your attention to the soles of your feet.Now, wiggle your toes. Feel your socks on the soles of your feet, focus on the arches of your feet. Go to the heels of your feet.Continue wiggling your toes.Now, open your eyes.Well done for doing this Soles of the Feet practice.

There are three SoF meditations, each one introduced to the participant in a particular order, each meditation is intended be repeated until the participant is able to follow the instructions with fluency. In published research, the training times for SoF were usually in two stages, the first, an intensive training period with a therapist, usually between 5 days and a week, followed by a longer period of self-practice (between 12 weeks and 2 years), often with an audio recording [32].
*SoF meditation (1)* Teaching Soles of the Feet meditation begins with the therapist asking the client to think of a happy situation and then following the steps of the meditation (see above).
*SoF meditation (2)* The participant then practises the same meditation, but this time whilst evoking a situation that make them feel angry.
*SoF meditation (3)* The participant then practises the meditation whilst thinking about a ‘trigger’ situation that typically causes them to get angry. This is the ultimate aim of the intervention—that the participant is able to identify triggering situations and use Soles of the Feet meditation appropriately in situ, before they get angry.

Although the original, core SoF practices [23] will be used, there will also be adaptions to the current manual, the main difference is that psycho-educational components around anger and stress reactions in the body will be added. The UMAA-LD SoF protocol will be designed as an addendum to the existing manual, rather than a replacement for it. The main additions will be as follows:
*UMAA-LD SoF will be designed specifically for use in NHS settings.* The SoF manual [23] does not specify what content is covered on a session-by-session basis. The UMAA-LD SoF manual will provide specific outlines for each of six sessions. Each session will take up to 90 min, with the clinician pacing the session to meet participants’ needs. See Table 1 for a typical session format.
*UMAA-LD SoF will provide educational materials* suitable for people with ID that will focus on anger, aggression, and mindfulness. These will be used in sessions and also form a ‘pack’ that the participant can take home and read.
*UMAA-LD SoF sessions will require the participant (with carer support) to engage in short, daily home meditation practices each week.* The home practices given will follow the progression of the session. A CD/audio file that will have a recording of the Soles of the Feet meditation will be provided in a format best suited to the participant. These audio recordings of SoF practices will be specially designed for the ID population and will last for around 4–6 min each.

**Table 1 Tab1:** Typical format for a UMAA-LD SoF session

Content of session	Approximate time frame (min)
Introducing the session	5–10
Review homework log	5–10
Psycho-educational component, i.e. what is anger? What is mindfulness?	20–30
Comfort break	5–10
Soles of the Feet meditation practice	20–30
Review of the session and home practice setting for next week	5–10

### Mindfulness scale for people with ID

To address aim 2, the following methodology will be adhered to.

The MAIDS will be a self-report measure to elucidate mindfulness processes in relation to problem areas, such as anger. Development of items will be informed by three sources: (1) examination of existing mindfulness measures (no current measure exists for use with people with ID), (2) research on the development of self-report measures for people with ID, and (3) consultation with mindfulness and ID professionals. To date, a working version of MAIDS (consisting of ten items) has been developed. The MAIDS will be incorporated in the UMAA-LD SoF protocol to test its feasibility as an evaluation tool.

The MAIDS will be tested on the 20 participants in the intervention study, at all three time points. In addition, to help determine reliability and validity of the scale, 80 further participants with ID will be recruited to complete the MAIDS, the Modified Overt Aggression scale [43], Novoco Anger Scale [44], Glasgow Anxiety [45] and Glasgow Depression Scale [46] at a single time point. Participants will be recruited from various sources, including local ID groups and residential homes. Informed consent will be gained prior to collecting data and will be collected by researchers visiting the participants to assist where required.

### Measures

A researcher is responsible for collecting all feasibility data and outcome measures. The primary aim of these outcome measures is to test the suitability and practicality of the measures with adults with ID. Following the initial screening visit, where capacity to consent is assessed, a baseline visit will be arranged prior to the commencement of the intervention where demographic information on age, gender, and current residential status will be gathered. All of the feasibility outcome measures described below will be taken at the three time points of baseline, 2 months post-baseline, and 6 months post-baseline.

#### Feasibility process measures

To address aim 1, the following measures will be taken.Screening and recruitment rates will be monitored.The MAIDS to measure skills in using mindfulness to manage anger.Data on adherence to mindfulness home practice.Participant drop out from the feasibility study will be closely monitored and reasons gathered where possible.An assessment of the completion rates of the questionnaires will be completed. This will encompass an analysis of any missing data patterns.Information gleaned from the qualitative interviews will be used to inform understanding of the process.Intervention fidelity will be monitored. Two out of six sessions with each participant will be audio recorded. One will be from the start of the intervention (sessions 1–3) and the other from sessions 4–6. The recordings will be evaluated using an adaptation of Singh’s Soles of the Feet monitoring form that evaluates adherence to the Soles of the Feet manual [23].A clinical input questionnaire will capture the participants’ recent clinical input (e.g. from a behavioural specialist, any other direct psychological interventions) and be completed by the carer with the researcher during the consent visit, this is repeated during the baseline visit to identify any recent changes.

#### Demographic measures

Following the initial screening visit, where capacity to consent is assessed, a baseline visit will be arranged prior to the commencement of the intervention where demographic information on age, gender, and current residential status will be gathered. As part of the inclusion criteria, the presence of an ID will be confirmed at baseline using two measures: (1) Wechsler Abbreviated Scale of Interlligence-Second Edition [41] that measures IQ in adults and (2) Adaptive Behaviour Assessment System® (ABAS)—Second Edition [42] that is completed by the carer and measures abilities, skills and physical, and sensory impairments.

#### Measures (administered to the participant with ID)

All of the potential outcome measures described below will be taken at the three time points of baseline, 2 months post-baseline, and 6 months post-baseline.

All self-report measures used have been adapted for use with an ID population or have been evaluated by the research team and are likely to be appropriate measures for use with individuals with ID.
*Novaco Anger Scale (NAS):* A 60-item scale exploring how an individual experiences anger, with three subscales: cognitive, arousal, and behavioural, that constitute a total score for anger disposition [44].
*Provocation Inventory (PI):* A 25-item scale that identifies the kinds of situations that induce anger in particular individuals [47].
*The Glasgow Depression Scale for adults with Learning Disabilities (GDS-LD):* A 20-item scale that asks how often depressive symptoms have occurred over the past week [46].
*The Glasgow Anxiety Scale for adults with Intellectual Disabilities (GAS-ID):* A 27-item self-rating scale that assesses how often anxiety symptoms have occurred over the past week [45].
*EQ-5D-Y (Youth version of the EQ-5D generic Health Related Quality of Life questionnaire: HRQoL):* This is a standardised and validated instrument on HRQoL and is intended for use with children and adolescents aged between 7 and 12 years old [48, 49]. There are currently no generic quality of life questionnaires adapted for people with ID.
*CHU-9D (A paediatric generic preference based measure of HRQoL):* This is intended for use with children aged 7–17 years [50]. There are currently no generic quality of life questionnaires adapted for people with ID and challenging behaviour.
*ICECAP-A (ICEpop CAPability measure for Adults):* A measure of capability for the general adult (18+) population for use in economic evaluation [51].

